## **7.12. In case of RCT, process of randomization and blinding, description of stopping rules for individuals for part of the study or entire study, the procedures and conditions for breaking the codes etc.**

The dietitians and enumerators will explain the purpose of the study to the participants and those participants who willing to give written informed consent and meet the inclusion criteria will be randomly assigned to either the intervention or the usual care arm. Once participants sign an informed written consent form, he or she will be enrolled in the study. Eventually, participants will be enrolled in either intervention or control groups randomly using computer generated random numbers.

## **7.13. A graphic outline of the study design and procedures using a flow diagram including the timing of assessments.**

Figure 1. Study design

[figure not shown]

# **Plan for data management and statistical analysis**

- **Data entry:** A data entry program will be developed using EpiData version 3.0. A number of skips and ranges will be developed to ensure data entry. Trained data entry professionals will enter the data. After the data entry, a thorough check and cleaning of data will be done to maintain consistency.
- **Data analysis:** Data will be analyzed on an intention-to-treat analysis. Data will be analyzed using STATA/MP version 14.1 (StataCorp LP, College Station, Texas). A number of statistical analysis will be done to analyze the data which are listed below:
- **Normality test:**The normality of data will be assessed using the Kolmogorov-Smirnoff test and visual inspection of Q-Q plots. Normally distributed data will be presented as means with standard deviation whereas non-normally distributed data will be expressed as medians with interquartile ranges.
- **Descriptive statistics**: Descriptive statistics will be carried out for socio-demographic information. Frequency, percentage, mean (standard deviation) and median (inter-quartile range) will be calculated under descriptive statistics.
- **Chi-square test**: Chi-square or Fisher exact test will be used to analyze between the intervention and usual care arm for categorical variables.
- **Independent sample t-test:** Difference between intervention and usual arm will be applied using independent sample t-test assuming equal variance if data is normally distributed for continuous variables (two-tailed; parametric).
- **Mann-Whitney U test**: Mann-Whitney U test will be used to compare the medians of continuous variables if in case the assumption for independent sample t-test will be violated (two-tailed; non-parametric).
- **Linear regression**: A linear regression analysis will be used to model the primary and secondary outcome measures.

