# **Project summary (~250 words)**

Diabetes mellitus is one of the major intractable public health problems in developing countries including Nepal. The dietary approach is of paramount significance in the management of type 2 diabetes. There is still a lack of evidence on a dietitian-led dietary approach to the management of T2DM patients in the Nepalese context. The aims of this study is to examine the effectiveness of dietitian-led dietary approach to management of diabetes on reduction of HbA1c level, nutrition education score and macronutrient intake among T2DM patients in a tertiary care hospital in Kathmandu, Nepal.

The Dietary Approach to the Management of Diabetes (DIAM-D) trial is a hospital-based, open-label, two-armed, randomized control trial. A total of 156 participants with T2DM having HbA1c >6.5% will be enrolled in the study. Participants will be consecutively enrolled and assigned to receive nutrition education and counseling (NEC) and diet plan in the intervention group (n=78) and usual routine care in the control group (n=78) randomly. The NEC will be provided to participants on group session and the diet plan will be face-to-face individual basis at the time of enrollment and follow-ups will be done every month. Baseline data will be collected using a structured questionnaire for an interview and the biochemical tests will be measured. Baseline data will be collected at the time of enrollment, midline in three months and end-line data collection in 6 months. The primary outcome of the study will be a difference in mean change (from baseline, midline to 6 months) in the HbA1c level between the two study arms from baseline to end line. The secondary outcomes measure will be changed in biochemical and clinical parameters between the two arms at baseline midline to six months. Data will be entered using Epidata Software and transferred to the STATA/MP version 14.1 for further analysis. Data will be analyzed using an intention-to-treat basis. Independent sampele t-test will be used to estimates changes between the intervention and usual care arms.

**Key word:** Dietitian, Dietary approach, Management, Diabetes, Nepal

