**Tools and procedure**

- Screening checklist: This checklist entails information regarding inclusion and exclusion criteria.
- Baseline questionnaire: The study participants’ information on Socio-demographic, such as age, sex, occupation, educational level, residence, religion, ethnicity, etc. will be taken by using a face-to-face structured questionnaire interview. The questionnaire will be adopted from NDHS 2017 and STEP Survey 2019^22,23^.
- Dietary intake: Dietary intake assessment will be assessed before intervention (baseline) and after intervention (end line) using 24-hour qualitative dietary recall and food frequency questionnaire (FFQ) to compute the macronutrient intake level.
- Biochemical measurements: A fasting blood sample for HbA1c, fasting glucose, liver function test (bilirubin, ALT, AST ALP, and albumin) and lipid profile (total cholesterol, triglycerides, HDL, LDL) will be measured at baselines, three months and six months. All blood samples will be taken and handled, analyzed and disposed of according to local practice policy.
- Quality of life: The Problem Areas in Diabetes (PAID) score^24^, a 20 items questionnaire measuring the problems related to emotions, treatment, food and social support, will be measured at baselines and 12 months.
- Physical measurement: Height will be measured using a stadiometer to the nearest 1cm. Participants' weight will be measured to the nearest 0.1kg using the Seca weighing scale. BMI will be measured calculated using the widely used formula (BMI= weight (kg)/height (m)^2^), and waist Hip Circumference (WHR) will be measured using measuring tape. Systolic and diastolic blood pressure will be measured three times after 5 minute seated rest using a sphygmomanometer and stethoscope. The trained data enumerator will be taking physical measurements according to the study manual procedures.
- Nutritional knowledge score on diabetes: The diabetes knowledge test (DKT)^25^will be used to assess the nutritional knowledge score on diabetes.
- Physical activity: The physical activity will be measured using the Global Physical activity questionnaire recommended by WHO STEPwise surveillance tools^23^.
- Monitoring checklist: This will be used as every month follow up checklist. The information on lifestyle modification such as consumption of food, physical activities, adherence, and diabetic-related minor and major complication will be sought.

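### No single primary HbA1c analysis is named: a normality check chooses between a t-test on change and Mann-Whitney, and an unspecified regression stands beside them

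*Protocol*

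**What the plan says.** The Project summary sets the outcome: "The primary outcome of the study will be a difference in mean change (from baseline, midline to 6 months) in the HbA1c level", compared between the two arms. It then names the test: "Independent sampele t-test will be used to estimates changes between the intervention and usual care arms".

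The section Plan for data management and statistical analysis sets the route to that test:

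- Normality check: "The normality of data will be assessed using the Kolmogorov-Smirnoff test and visual inspection of Q-Q plots".
- If it is passed: "Difference between intervention and usual arm will be applied using independent sample t-test assuming equal variance if data is normally distributed for continuous variables".
- If it is not: "Mann-Whitney U test will be used to compare the medians of continuous variables if in case the assumption for independent sample t-test will be violated".
- As a separate item, with no covariates and no rank: "A linear regression analysis will be used to model the primary and secondary outcome measures".

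Under Tools and procedure, HbA1c and the other blood tests "will be measured at baselines, three months and six months". The Sample size section expects 25% loss to follow-up and drop-out, and the analysis is to be by intention to treat.

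**The concern.** Three analyses are listed for the primary outcome and none is named as the one that decides the trial. The choice between the first two rests on the trial's own data and partly on a visual judgement. The Protocol does not say which variable is checked (HbA1c or its change, pooled or by arm), at what level, or what happens if the test and the plot disagree.

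The branches do not answer the same question. A t-test on change estimates the stated outcome, a difference in means. Mann-Whitney tests whether a value from one arm tends to exceed a value from the other. It compares medians only under extra conditions, such as a pure shift between arms, so the statement "Mann-Whitney U test will be used to compare the medians of continuous variables" misdescribes it in general. The trial could thus report a result for something other than its declared outcome, for a reason settled only after the data are seen.

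An unadjusted t-test on change is also not the most precise use of a baseline value that is already collected.

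**Working it through.** **1. Inputs.** From the Sample size section: two-sided 5%, 90% power, 54 per arm before inflation, printed S = 0.1 and d = -0.64, source means 9.67 and 10.30 (difference 0.63). Not in the Protocol, so assumed: the HbA1c SD at each visit and rho, the correlation between baseline and 6-month HbA1c.

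**2. The plan's own figure.** n per arm = 2(1.96 + 1.282)²S²/d².

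- S = 0.1, d = 0.64: 2 × 10.51 × 0.01/0.4096 = 0.51, that is 1 per arm, not 54.
- S = 1.0: 51.3 (52 per arm) at d = 0.64 and 53.0 (53 per arm; 54 with the t distribution) at d = 0.63.

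The stated 54 is reached only with an SD of about 1.0, so SD 1.0 is used below as an assumption.

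**3. Precision, equal SD s at both visits.** The variance of change is 2(1 - rho)s². The residual variance after baseline adjustment (ANCOVA) is (1 - rho²)s². The ratio is (1 + rho)/2. Power is from the noncentral t with SD 1.0, d 0.63 and 54 per arm.

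| rho | Variance ratio | Power, change t-test | Power, ANCOVA |
|---|---|---|---|
| 0.3 | 0.65 | 78% | 93% |
| 0.5 | 0.75 | 90% | 96% |
| 0.7 | 0.85 | 98.7% | 99.5% |
| 0.9 | 0.95 | near 100% | near 100% |

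At rho 0.5, 54 per arm is worth 54/0.75 = 72.

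**4. Precision, smaller baseline SD.** The entry limits (HbA1c above 6.5% at diagnosis, exclusion from 10.5%) may narrow the baseline spread. With k the ratio of baseline to 6-month SD, the variance ratio is (1 - rho²)/(1 + k² - 2·rho·k). For k = 0.7 (assumed):

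- rho 0.3: 0.91/1.07 = 0.85
- rho 0.5: 0.75/0.79 = 0.95
- rho 0.7: 0.51/0.51 = 1.00

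**5. The 3-month value.** With complete 6-month data, a repeated-measures model with baseline adjustment is exactly as precise as ANCOVA for the 6-month difference (ratio 1.00). With 25% missing at 6 months, all of them seen at 3 months (best case), the ratio to ANCOVA runs from 0.94 to 0.89 over assumed correlations (baseline to 3 months, baseline to 6, 3 to 6) from (0.5, 0.4, 0.6) to (0.8, 0.7, 0.85). That is a further saving of about 6 to 12%.

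**6. How often the check would fire.** Simulated at 5% with 108 values and 1,500 replicates:

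| Data | Plain Kolmogorov-Smirnov | With Lilliefors correction |
|---|---|---|
| Normal | 0% | 4% |
| Lognormal, sigma 0.3 | 7% | 60% |
| Lognormal, sigma 0.5 | 48% | 95% |

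Which branch is taken thus depends on a detail of the test that the Protocol does not fix.

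**7. What the switch changes.** Suppose only a fraction of the intervention arm responds, with a mean effect of about 0.64 SD. At 20% responders the difference in medians is 0.31 and the Mann-Whitney-type shift 0.43. At 30% they are 0.51 and 0.58. At 50% all three agree at about 0.62.

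**The case against.** The strongest defence is that a t-test on change matches the declared outcome and is unbiased under randomisation. The switch also has little effect on significance. At 58 per arm with plain Kolmogorov-Smirnov, the share of simulated trials in which the check fired and the significance verdict changed was 0% for normal data, at most 0.4% for gamma with shape 4, at most 0.6% for t with 5 degrees of freedom, and 0.7 to 2.6% for gamma with shape 2. Type I error stays near 5%. All of this stands, although the Q-Q judgement was not simulated. It limits the complaint to what is estimated and to which analysis counts.

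Three stronger readings are tempting, and the Protocol does not support them.

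- A reader might infer that the plan wastes the baseline value. A change score uses it, though inefficiently. The Study variables section names HbA1c as the dependent variable and also lists it among the independent ones, so the regression may well be meant to adjust for baseline. The defect is that the Protocol does not say so and gives the regression no rank.
- A reader might infer a completers' analysis under an intention-to-treat label. No text says that patients without a 6-month value are dropped, and missing-data rules are commonly left to an SAP, which is not at hand.
- A reader might infer that the 3-month data are needed for precision. They help the 6-month contrast only when 6-month values are missing.

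**Conclusion.** The point holds in a limited form. The Protocol lists a t-test, Mann-Whitney and a regression for the primary outcome, designates none, and lets a normality check choose between the first two. The fallback can leave the declared difference in mean change. In the responder example, a mean effect of about 0.64 SD corresponds to a median difference of only 0.31. This is a problem of estimand and pre-specification, not of inflated false positives.

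Baseline adjustment is asymptotically never less precise than the change-score t-test, at the price of about one degree of freedom. The size of the gain is uncertain: 5 to 35% of the variance for rho from 0.9 down to 0.3 with equal SDs, but 15%, 5% and nothing at rho 0.3, 0.5 and 0.7 if the baseline SD is 0.7 of the 6-month SD. The power figures rest further on an SD of 1.0, where the Protocol prints 0.1. The case for one named analysis does not depend on any of these assumptions.

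**What to change.** Name one primary analysis in the statistical section and repeat it in the Project summary: linear regression of 6-month HbA1c on arm and baseline HbA1c, with robust standard errors in place of the equal-variance assumption, reporting the adjusted mean difference with its 95% confidence interval. Adjusted for baseline, this coefficient is the same whether the response is 6-month HbA1c or its change, so the declared outcome is kept.

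Delete the normality check as a decision rule for the primary outcome. Keep Mann-Whitney as a labelled sensitivity analysis and remove the statement that it compares medians.

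Optionally, because 25% loss is expected, use a mixed model for HbA1c at 3 and 6 months with arm, visit, arm-by-visit and baseline HbA1c, and take the 6-month contrast as primary. Patients with only a 3-month value then contribute.

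The cost is wording. No extra patients, visits or measurements are needed.

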# **Biases**

Due to the educational experimental study, selection bias can occur during the selection of control and intervention group. To minimize the selection bias, the randomization procedure will be strongly followed. Similarly recall bias can occur, while asking the question. To minimize it, proper probing will be carried out. Likewise, interviewer bias can occur, to minimize it length of time taken to interview the average intervention and the average control will be noted.

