## **7.10. Tools and techniques for data collection**

The baseline and end-line data collection will be performed in both intervention and usual care arm. A pre-tetsed culturally accepted and adapted, Nepali translated version tools and techniques will be used to conduct the study. A total of three data collection team who have graduated in health or nutrition science will be hired from the local area.

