# **Limitations of the study**

In this study, the participants will be enrolled from OPD basis, so, we cannot resolve the adherence of dietary advice to all participants. Similarly, there may be a recall bias to collect 24-hour dietary recall and may have social desirability bias for collecting behavioral related history. To minimize recall bias, proper probing will be carried out. Likewise, interviewer bias can occur, to minimize it the length of time taken to interview the average intervention and the average control will be noted. Selection bias can occur during the selection process. We will strongly follow randomization to the selection of intervention and usual care arms by a trained data enumerator so that this will minimize the confounding. Also, the cross-contamination may occur between intervention and control arms. We will suggest the participants from the intervention arm not to share the provided information with the others to prevent cross contamination.

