**Data collation phase**

- Firstly, thesis writing students will be trained for data collection procedure, participants’ selection and randomization. The manual of data collection will be developed and distributed to the enumerators and study team members. Conduct a week-long training workshop to the data enumerators and dietitian regarding data collection techniques and diet counseling. The study questionnaire, anthropometric instruments, biochemical instruments will be pre-tested. Pre-testing should be conducted in order to maintain the accuracy and clarity of tools.
- Nutritional counseling and diet plan guidelines will be pre-tested in another hospital not included in the study area. Pre-tested guidelines will be approved by a multi-disciplinary expert team.
- After pre-testing all the ambiguous, misleading and wrongly interpreted questions will be omitted and the questionnaire will be revised in accordance with the findings of pre-testing. Instruments such as biochemical tools and clinical tools will be regularly calibrated before use.
- Supervision and monitoring during the data collection will be done by the investigators.
- Confidentiality while taking the interview will be maintained in order to avoid bias.
- The core study team will be made responsible to maintain the appropriateness of sampling and data collection techniques. Interviews will be conducted into the local language and the responses will be coded simultaneously on the questionnaire. The filled-in questionnaire will be checked and edited each day by the supervisor at the data collection sites.
- The data collection will be carried out in close supervision of the research team. In order to maintain the quality of the data collection, the investigators will make at least 10% accompaniments and 20% back checks every day. Any error in data collection will be recorded in the investigator logbook and the enumerators will be informed of the errors and suggested the improvement measures.
- All the filled-up questionnaires will be safely stored in a locker.

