**Main Study Questionnaire in English - Baseline/End line**

| **Participants Information** | | | |
| --- | --- | --- | --- |
|  | Response | | Code |
| Study Group | Control 0  Intervention 1 | |  |
| Date |  | |  |
| Participants ID |  | | I1 |
| Participants full name |  | | I2 |
| Contact number |  | | I3 |
| Baseline interview date |  | | I4 |
| Follow-up date |  | | I5 |
| End line interview date |  | | I6 |
| Consent has been read and obtained | Yes  No | 1  2  If no, End | I7 |
| **Section 1: Socio-demographic information, Baseline** | | | |
| Sex ( record male/female as observed) | Male  Female | 1  2 | C1 |
| How old are you | …….years |  | C2 |
| What is your education level? | No formal education  Primary (1-5)  Secondary (6-10)  Higher secondary(11-12)  Bachelors and above  Refused | 1  2  3  4  5  88 | C3 |
| What is your ethnic background?  (Refer to caste classification: CC1 ) | Dalit  Disadvantaged Janajati  Relatively advantaged Janajati  Disadvantaged Non-dalit Terai caste group  Religious minorities  Upper caste group  Others  Refused | 1  2  3  4  5  6  7  88 | C4 |
| What is your religion? | Hindu  Buddhist  Muslim  Kirat  Christian  Others  Refused | 1  2  3  4  5  6  88 | C5 |
| What is your marital status? | Never married  Married  Separated/divorced  Widowed  Cohabiting  Refused | 1  2  3  4  5  88 | C6 |
| Which of the following best describes your main occupation? | Government employee  Non-government employee  Self-employed  Students  Homemaker  Retired  Unemployed  Others  Refused | 1  2  3  4  5  6  7  8  88 | C7 |
| Where do you live? | Urban  Rural | 1  2 | C8 |
| How much is your average monthly Income? | Rs | ……… | C9 |
| Family history of Diabetes Mellitus | Yes  No | 1  2 | C10 |
| **Section 2: Behavioral information Baseline/Endline** | | | |
| **Tobacco use** | | | |
| Do you currently smoke any tobacco products, such as cigarettes, bidis, cigars, pipes, hukahs, or tamakhus? | Yes  No | 1  2  If No, go to A1 | T1 |
| How frequently do you smoke tobacco products? | Daily  5-6 days a week  3-4 days a week  1-2 days a week  Occasionally | 1  2  3  4  5 | T2 |
| In the past, did you ever smoke any tobacco products? | Yes  No | 1  2  If No, go to A1 | T3 |
| In the past, how frequently did you smoke tobacco products? | Daily  5-6 days a week  3-4 days a week  1-2 days a week  Occasionally | 1  2  3  4  5 | T4 |
| **Alcohol consumption** | | | |

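### The end-line interview form shows the arm, enumerators are described as helping to allocate, and the one measure named against interviewer bias records it rather than prevents it

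*Protocol*

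**What the plan says.** - **Measure against interviewer bias.** Biases states: "interviewer bias can occur, to minimize it length of time taken to interview the average intervention and the average control will be noted". The same measure appears, almost word for word, under Limitations of the study: "interviewer bias can occur, to minimize it the length of time taken to interview the average intervention and the average control will be noted". No other measure is tied by name to interviewer bias.
- **The form.** The instrument is titled "Main Study Questionnaire in English - Baseline/End line", and its first field is "Study Group | Control 0 Intervention 1".
- **Who allocates.** Limitations of the study says: "We will strongly follow randomization to the selection of intervention and usual care arms by a trained data enumerator". Under Plan for supervision and monitoring, the data collation phase says: "thesis writing students will be trained for data collection procedure, participants’ selection and randomization". Budget item A3 has those students working as enumerators. Section 7.12 mentions computer-generated random numbers but not who holds or applies them.
- **Who measures.** Section 7.10 gives the physical measurements to the trained enumerator, with blood pressure read by sphygmomanometer and stethoscope. The 24-hour recall, PAID, knowledge, dietary adherence and activity sections are all part of the same questionnaire.
- **Blinding.** Section 7.2 calls the trial open-label. The heading of 7.12 asks for blinding, but its text says nothing about outcome assessors.
- **Staff.** Section 7.10 states: "A total of three data collection team who have graduated in health or nutrition science will be hired". The design phase text instead describes the enumerators as final-year students, and the budget funds two of them.

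**The concern.** An open-label design means that participants and the dietitian know the arm. It does not require the person collecting outcomes to know it. Here the collector is told the arm by the form before asking the first question, and may already know it from allocation.

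The Research questions/hypothesis section names nutrition knowledge and macronutrient intake beside HbA1c. Macronutrient intake rests partly on a 24-hour recall. Both Biases and Limitations of the study rely on probing to limit recall bias. Probing is at the interviewer's discretion, so it can differ between arms when the arm is known. A stethoscope reading of blood pressure also depends on the observer. At stake is whether a difference between arms in these outcomes can be credited to the intervention.

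**Working it through.** The protocol gives no figure on this point, so the check is mainly a comparison of sections.

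**1. Can the interviewer see the arm?** Yes, from the form itself. It serves at baseline and end line and opens with the study group. The protocol does not say when, or by whom, that field is completed.

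**2. Are collectors involved in allocation?** They are described so in two places: Limitations of the study (allocation by an enumerator) and the data collation phase (students trained in randomization), with Budget item A3 identifying the students as enumerators. No section says that whoever allocates a participant also interviews that same participant at end line.

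**3. Does the named measure prevent bias?** No. Average interview length by arm could show that one arm was interviewed for longer. It would not stop or correct uneven prompting, lenient coding or a biased pressure reading, any of which can happen in interviews of equal length.

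**4. Do other measures fill the gap?** The data collation phase plans a week-long training, a manual, daily checking of forms, 10% accompaniments, 20% back checks and confidential interviews. These supervise conduct in general. None hides the arm.

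**5. Which outcomes are exposed, and how much?**

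| Outcome | How it is obtained | Room for interviewer influence |
| --- | --- | --- |
| 24-hour recall | Open entries, with probing | Largest |
| Blood pressure | Three manual readings by stethoscope | Substantial |
| Knowledge items | Yes / No / I don't know | Smaller |
| PAID | Fixed 0 to 4 scale | Smaller |
| Activity | Structured questions | Smaller |
| HbA1c | Laboratory value | Little |

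**6. Illustration under an assumption.** Suppose there is no true effect, but knowledge of the arm shifts the measured difference by b standard deviations. The protocol gives no value for b; the range is assumed. With n per arm, a two-sided 5% comparison of two means rejects with probability

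1 − Φ(1.96 − λ) + Φ(−1.96 − λ), where λ = b / √(2/n).

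For b = 0.2 and n = 54: √(2/54) = 0.192 and λ = 1.04, so the probability is about 0.18.

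| b (assumed) | n = 54 per arm | n = 78 per arm |
| --- | --- | --- |
| 0 | 5% | 5% |
| 0.1 | 8.1% | 9.6% |
| 0.2 | 18.0% | 23.9% |
| 0.3 | 34.4% | 46.6% |

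The two values of n are the calculated and inflated sizes per arm in the Sample size section. The table shows how sensitive a comparison would be to a shift of a given size. It is not evidence that such a shift will occur.

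**The case against.** The case on the other side has several parts.

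- **Other quality controls exist.** A reader might infer that interview length is the only protection in the plan. It is not. Accompaniments, back checks, training, structured tools and repeated blood pressure readings all discipline interviewing. What stands is narrower: interview length is the only measure named against interviewer bias, and none of the others masks the arm.
- **Direction is not established.** It is tempting to say that every such bias favours the intervention. The protocol does not support that. It does not define which change in macronutrient intake counts as improvement, and more probing in one arm could raise reported intake.
- **The overlap of roles is partly inferred.** Section 7.12 does not say who applies the random numbers, and the sentence in Limitations of the study is ambiguous. This objection stands against any claim that each interviewer allocated the participants whom he or she later assesses. It does not affect the arm field on the form.
- **Staffing is uncertain.** A reader might take three collectors plus a dietitian as proof that masking needs no extra staff. The protocol conflicts on this: three hired graduates in 7.10, but final-year students elsewhere, with two budgeted. One student's thesis concerns the effectiveness of the education materials, so that student may know the arms anyway. Removing the field needs no staff under either description; a full separation of roles may not be feasible.
- **Masking is incomplete.** Participants know their arm, and the protocol already admits social desirability bias. Masking interviewers would not remove it.
- **The primary outcome is hardly touched.** HbA1c is the only dependent variable listed in 7.8 and is a laboratory value. This stands and limits the weight of the point.

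**Conclusion.** The point holds in a limited form and is worth acting on as a cheap improvement. The arm is visible on the outcome form, collectors are described as taking part in allocation, and the named measure may detect unequal interviewing but does not prevent bias. The exposure is chiefly in dietary recall and manual blood pressure, and smaller in the knowledge, PAID and activity items.

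Size and direction cannot be determined from the protocol; the rejection rates shown rest wholly on an assumed shift. A reader might infer that the HbA1c comparison is compromised. Nothing in the protocol supports that through this route. The conclusion assumes that the form will be used as printed and that no masking procedure exists beyond what the protocol describes.

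**What to change.** 1. Remove the study-group field from the interview form and link the arm by participant ID at analysis.
2. Have the allocation list held by someone who neither recruits nor assesses outcomes. This should be neither the dietitian nor an enumerator, because 7.12 has both explaining the study to candidates before assignment. Giving either the list would weaken allocation concealment, which does bear on the HbA1c comparison.
3. As far as the existing team allows, have end-line interviews and blood pressure done by a team member who did not allocate or counsel that participant. Reconcile the descriptions of the enumerators so that it is clear what the team can cover.
4. Record at end line whether the interviewer learned the arm.
5. Keep interview length as a supplementary check between arms, not as the safeguard.

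The cost is a form edit, a named holder for the list and a task rota. The rota brings some scheduling constraint. Some participants will reveal their arm and their own reporting bias will remain, so the change reduces the problem without removing it.
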